# 12. Statistic analysis

## 12.1 Tabulation of subject background

The subject background will be tabulated by group.

## 12.2 Analysis of gene expression profile

Compare the data on gene expression profile obtained before and after the study drug administration (days of evaluation at Week 0 and Week 8) by dose (300 mg/day and 600 mg/day) and by patient. The details about the method of analysis of the gene expression profile are presented in the “Manual for determination of the gene expression profile of NIK-333.”

It may become necessary to make additional analyses focused on the NIK-333 response gene on the basis of the results of the present analysis of gene expression profile. In such cases, revise the “Manual for determination of the gene expression profile of NIK-333.”

## 12.3 Safety analysis

Prepare tabulated lists of adverse events (symptoms and signs, etc.), and tabulate the data by type and severity. Concerning laboratory tests, prepare tabulated lists and time-course charts, and calculate summary statistics. Tabulate other observation parameters in the same way as laboratory tests.

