| Related | Abdominal distension, Blood pressure increased, Urticaria, Abnormal sensation in eye, Hyperglycaemia, Duodenitis, Gastritis, Lip dry, Keratoconjunctivitis sicca, Oropharyngeal Pain, Malaise | 1 | 22 |
| Blood urine present,, Reflux oesophagitis, Hypertriglyceridaemia,  Gamma-glutamyltransferase increased | 2 |
| Headache | 3 |

List of adverse events in repeated administration (2)

| Dose | Causal relationship | Events | Number of events | Total |
| --- | --- | --- | --- | --- |
| 900 mg  (At the start n= 9)  * Discontinued during repeated administration | None | Vertigo, Abdominal pain upper, Joint swelling, Chest pain, Alanine aminotransferase increased, Aspartate aminotransferase increased, Blood lactate dehydrogenase increased, Varices oesophageal, Pyrexia, VIth nerve paralysis, Scar,Back pain, Protein urine, Oropharyngeal discomfort, Insomnia, Headache, Nausea | 1 | 23 |
| Nasopharyngitis | 6 |
| Related | Diarrhoea, Chapped lips, Abdominal pain upper, Retinal haemorrhage, Stomach discomfort | 1 | 26 |
| Dysgeusia, Abdominal pain, Protein urine present, Musculoskeletal stiffness | 2 |
| Urinary occult blood positive | 3 |
| Blood pressure increase | 4 |
| Headache | 6 |

Among the 9 subjects who moved on to repeated administration at Level 3, 1 subject was suspended from drug administration and 3 subjects were discontinued from the study due to increased blood pressure. In 1 subject who exhibited blood pressure increase, fundal haemorrhage was observed. However, the subject was placed on observation without requiring medical intervention.

The incidences of events suggesting the presence of effects on renal functions, such as protein urine and urinary occult blood, also increased as compared with Level 1 and Level 2. The numbers of subjects whose protein urine and urinary occult blood shifted to + or more after the start of repeated administration at each level are shown in the table below. Abnormal changes of protein urine and urinary occult blood after the start of repeated administration were also observed in subjects who showed no blood pressure increase, suggesting that NIK-333 affects renal functions.

Frequency of subjects exhibiting a shift to (+) after repeated administration at
each level

|  | Change  Dose | Level of change: From baseline | | | | |
| --- | --- | --- | --- | --- | --- | --- |
| None | 1 grade | 2 grades | 3 grades | 4 grades |

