Adverse events of particular clinical significance were not observed at Level 1 (300 mg group) and Level 2 (600 mg group), and tolerability was judged to have been confirmed. However, the gastric polyp observed at Level 1 was considered an event requiring endoscopic exam in the subsequent phases.

At Level 3 (900 mg group), blood pressure increase was observed in 4 out of 9 subjects during the period of 24 weeks from the start of repeated administration. Since this event was an unknown adverse reaction, and the mechanism of its onset has not been understood, administration of the study drug and enrollment of new subjects were discontinued. Although the symptom related to the event disappeared after pharmacotherapy, the extent shifted from the normal range to the range of severe hypertension in some subjects, prompting the event to be regarded as an important event that could have accompanying secondary inconveniences unless some treatment was given. Moreover, some subjects exhibited protein urine and urinary occult blood in association with blood pressure increase, and some subjects exhibited abnormal changes in protein urine and urinary occult blood without blood pressure increase. The frequency of the occurrence of abnormal changes in urinary qualitative parameters was high at Level 3. Furthermore, nail disorder, which is known to be induced by taking a large amount of retinoid, was seen in 2 subjects about 12 weeks after the end of administration. For these reasons, 900 mg was deemed inappropriate as a clinical dose.

The effect of NIK-333 on bone, which was seen in non-clinical studies, was not observed at any of the levels assessed.

2) Pharmacokinetics

There were no differences in the plasma concentrations of unchanged NIK-333 in the fed and fasted conditions.

The pharmacokinetic parameters (AUC0-24hr and Cmax) of unchanged NIK-333 in plasma were confirmed to exhibit linearity after single or repeated administration of 300 mg, 600 mg and 900 mg.

Since almost no unchanged NIK-333 and NIK-333 lipids form were seen in plasma at Week 48 of administration and Week 12 and Week 24 after the end of administration, the drug was not considered to be accumulated in the body during repeated administration.

Excretion of unchanged NIK-333 in urine was not seen after single administration.

3) Conclusions

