# 3. Study objectives

This 8-week repeated administration study compares the NIK-333 doses of 300 mg/day and 600 mg/day in patients who were completely cured of hepatitis C virus (HCV)-positive HCC by examining the changes in liver and peripheral gene expression profiles before and after administration of each dose and the drug concentrations in the liver and plasma. After the above test (liver biopsy), NIK-333 of 600 mg/day is administered to all subjects until Week 96 (88 weeks) to investigate safety, with a focus on the cardiovascular system, and the changes of plasma drug concentrations during long-term administration.

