## 5.3 Exclusion criteria

Patients who fall under any of the following criteria will be excluded.

[1] Patients positive for HBs antigen

[2] Patients showing portal infiltration of HCC on CT images

[3] Patients who have also undergone transcatheter arterial embolization therapy (TAE/TACE) as combination with the radical therapy

[4] Patients who have received other study drugs, anticancer drugs, interferons, or vitamin K2 after radical therapy

[5] Patients who have hypertension as a complication, and whose blood pressure cannot be controlled by drug therapy (systolic blood pressure of 160 mmHg or higher or diastolic blood pressure of 100 mmHg or higher, as determined at subject registration)

[6] Patients who have a history of allergy to CT contrast media, and whose participation in this study is judged to be inappropriate by the investigator or the subinvestigator

[7] Patients whose hemoglobin content is less than 8.0 g/dL and whose prothrombin time (%: activity value) is less than 40%, patients who are taking drugs with a potential of inducing blood coagulation abnormality, and patients who are judged to be ineligible for liver biopsy by the investigator or the subinvestigator

[8] Patients with a history of total gastrectomy

[9] Patients with serious complications (serious renal disorder, heart disease, diabetes mellitus, autoimmune disease, asthma, etc.)

[10] Patients confirmed of having another malignant neoplasm or who had undergone a radical therapy within the last 5 years to treat another malignant neoplasm (however, this does not apply to endoscopic resection and resection of intraepithelial carcinoma）

[11] Patients who are pregnant, who have a possibility of being pregnant or who have a desire to become pregnant during the study period

[12] Lactating women

[13] Patients who have a history of allergy to retinoid-related substances (vitamin A, etc.) in the past

[14] Other patients deemed ineligible to participate in the study by the investigator or the subinvestigator

[Rationale]

[1]: The subjects of the ongoing phase II/III study of NIK-333 are patients with HCV-positive HCC. Moreover, while the liver gene expression profiles reportedly are different between patients with HBV-positive hepatitis and patients with HCV-positive hepatitis, the virological background of the patients should be made uniform.

[2]: Because NIK-333 is not indicated for highly malignant HCC associated with portal infiltration

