Take body temperature (axillary), blood pressure (systolic/diastolic), pulse rate (dorsal position or sitting position) and body weight at 4-week intervals from the start of study drug administration (within 14 days before the start of administration) until the end of study drug administration, and at the time of follow-up examination.

If the study has been discontinued, body temperature (axillary), blood pressure (systolic/diastolic), pulse rate (dorsal position or sitting position) and body weight will be determined to the extent possible.

[6] Laboratory tests

Collect blood and urine samples and determine the following parameters at 4-week intervals from the start of study drug administration (within 14 days before the start of administration) until the end of study drug administration, and at the time of follow-up examination.

If the study has been discontinued, blood and urine samples will be collected and the following parameters will be determined to the extent possible.

1) Hematology tests: White blood cell count, red blood cell count, hemoglobin level, hematocrit, platelet count

2) Blood biochemistry tests: Total protein, serum albumin, serum bilirubin, total cholesterol, LDL cholesterol, HDL cholesterol, triglyceride, blood glucose, urea nitrogen, Cl, Na, K, Ca, ALP, AST (GOT), ALT (GPT), LDH, -GTP, choline esterase, serum creatinine, A/G ratio, free fatty acid, 2-microglobulin

3) Urinary tests (fresh urine): Qualitative (glucose, protein, urobilinogen, ketone body, occult blood), urinary albumin (converted to creatinine), urinary sediment (red blood cells, white blood cells, epithelial cells, casts, others), 2-microglobulin

[7] Blood pressure parameters

Collect blood and urine samples and determine the following parameters at 48-week intervals from the start of study drug administration until the end of study drug administration. If the systolic blood pressure exceeds 140 mmHg or the diastolic blood pressure exceeds 90 mmHg on two or more successive measurements, blood pressure parameters will be determined at the time of second or subsequent examination. However, determination of creatinine clearance, one of the blood pressure parameters, under increased blood pressure will be conducted to the extent possible.

1) Blood biochemistry tests: Renin activity, aldosterone, cortisol, uric acid, FT3, FT4, TSH, angiotensin II, hANP, BNP, catecholamine, growth hormone, dehydroepiandrosterone sufate (DHEAS)

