# 11. Treatment for subjects

Record any treatment other than drug therapy with the study drug given to the subjects, (e.g., a concomitant drug).

(1) Permitted treatment method

Treatments during the study drug administration period

During Step I, to the extent possible, avoid changing the type and dosage regimen of the drug, or discontinuing administration of the drug which the subject has been taking before the start of the study drug administration because gene expression may be affected. If concomitant use of any other drugs has become necessary, long-term administration should be avoided to the extent possible.

In Step II, there are no restrictions regarding the treatments other than those targeted to HCC, unless prohibited concomitant drugs and caution-required concomitant drugs are used.

However, if any other drugs are used during the study drug administration period, the name of the drug used, daily dose, route of administration, administration period and objectives of the use should be recorded.

(2) Prohibited or caution-required treatment methods

Treatments with the following drugs are designated as prohibited or caution-required concomitant treatments because they may interfere with efficacy evaluation of the subjects or assurance of safety. Moreover, concomitant use of both prohibited concomitant drugs and caution-required concomitant drugs is prohibited during the period from the day of the start of study drug administration until Week 8 after the start of administration because gene expression may be affected.

[1] Prohibited concomitant drugs and prohibited concomitant food: Administration and consumption of the following drugs and food are prohibited during the study drug administration period.

|  | Drug classification | Generic name | Brand name |
| --- | --- | --- | --- |
| 1 | Other study drugs |  |  |
| 2 | Anticancer drugs | All anticancer drugs including 5FU, MMC, DXR and tretinoin | |
| 3 | Natural interferons | Interferon α | OIF, Sumiferon |
| Interferon β | IFN β, Feron |
| 4 | Genetically-modified interferons | Peginterferon-α-2a | Pegasys |
| Interferon α-2b | Intron A |
| Peginterferon-α-2b | Pegintron |
| Interferon alfacon-1 | Advaferon |
| Interferon β-1a | Avonex |
| Interferon β-1b | Betaferon |
| 5 | Vitamin K2 | Menatetrenone | Glakay, Kaytwo |
| 6 | Retinoid | Etretinate | Tigason |
| 7 | Vitamin A | Cod-liver oil | Cod-liver oil |
| Retinol palmitate | Chocola A |

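### Step II is built around cardiovascular safety, but the blood pressure summaries fixed in 12.3 could understate a rise once antihypertensives start or subjects stop

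*Protocol*

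**What the plan says.** Protocol section 3 gives the purpose of Step II as "to investigate safety, with a focus on the cardiovascular system". Section 4.4 (rationale for the Step II period) ties this to the blood pressure effect at 900 mg/day.

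Section 12.3 first asks for adverse events to be listed and tabulated by type and severity. It then says: "Concerning laboratory tests, prepare tabulated lists and time-course charts, and calculate summary statistics. Tabulate other observation parameters in the same way as laboratory tests". Blood pressure falls under the other observation parameters. Section 12.7 (5) leaves missing vital signs as missing.

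On other treatment, section 11 (1) says: "In Step II, there are no restrictions regarding the treatments other than those targeted to HCC", apart from the listed prohibited and caution-required drugs. No antihypertensive is on either list. Step I differs: changes to existing medication are to be avoided where possible. Drug name, dose, route, period and purpose are recorded throughout.

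On phase I at 900 mg, section 2.3 reports that among 9 subjects "1 subject was suspended from drug administration and 3 subjects were discontinued from the study due to increased blood pressure". It adds: "Although the symptom related to the event disappeared after pharmacotherapy". The repeated-dose adverse event tables in the same section also list blood pressure increase as drug-related once at 300 mg and once at 600 mg. The 600 mg entry begins: "Abdominal distension, Blood pressure increased, Urticaria".

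**The concern.** A visit mean describes the subjects still attending, on whatever treatment they then take. If a rise prompts an antihypertensive or a stop, the affected readings fall back or disappear, and the curve flattens when the effect is present. Section 12.3 does not connect the blood pressure summaries with antihypertensive use or with stopping, although both are recorded. A time-course chart read alone could then be too reassuring on the main safety question of the 88-week extension.

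The risk background has a related weakness. A reader of 2.2, the conclusions of 2.3, or 2.4 would not learn that drug-related blood pressure increases were listed at both doses used in this trial.

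**Working it through.** The plan states no blood pressure effect, SD, power or precision. The 12 subjects (6 + 6) are justified by feasibility in 12.6, so there is no planned figure to reproduce. The checks below test the mechanism.

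**1. Understatement of the mean.** Suppose k of 12 subjects rise by R mmHg and the others do not change. Antihypertensives lower a treated responder by a. R, a and k are assumptions.

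- True mean change = k × R / 12.
- Observed mean change = (treated responders still present) × max(R − a, 0) / (subjects still present).

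With k = 4 and R = 30, the true mean is 4 × 30 / 12 = +10.0.

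| What happens to the 4 responders | a = 10 | a = 20 | a = 30 |
| --- | --- | --- | --- |
| All treated, none leave (n = 12) | 4 × 20 / 12 = +6.7 | 4 × 10 / 12 = +3.3 | 0.0 |
| Two leave, two treated (n = 10) | 2 × 20 / 10 = +4.0 | 2 × 10 / 10 = +2.0 | 0.0 |
| All leave (n = 8) | 0.0 | 0.0 | 0.0 |

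Over R = 20 to 40 and k = 1 to 5, the true mean runs from 20 / 12 = +1.7 to 5 × 40 / 12 = +16.7. In every case the observed mean can fall to 0.

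**2. Subjects left at late visits.** Confirmed recurrence ends participation (10.1). Section 2.2 gives recurrence of 24% at 1 year and 76% at 3 years, and 96 weeks is 96 × 7 / 365.25 = 1.84 years.

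- One-year rate held constant: 12 × 0.76^1.84 = 7.2.
- Three-year rate held constant: 12 × 0.24^(1.84/3) = 5.0.
- Piecewise: 12 × 0.76 × (0.24/0.76)^(0.84/2) = 5.6.

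So about 5 to 7 of 12 would remain. This assumes the quoted rates apply from first dose and that the drug does not alter them. For comparison, 7 of 12 subjects remained at the end of 48 weeks at 600 mg in phase I.

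**3. What the adverse event table protects.** The chance of at least one blood pressure case among 12 is 1 − (1 − p)^12.

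- p = 4/9 (900 mg in phase I): 99.9%.
- p = 2/12: 89%.
- p = 1/12 (one related event among 12 starters at 600 mg, taken as one subject): 65%, so a 35% chance of no case.

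**4. The phase I texts side by side.** The tables count events per named term. At 600 mg the related events are 11 × 1 + 4 × 2 + 3 = 22, which matches the printed total. At 300 mg they are 20 × 1 + 2 × 2 + 5 = 29, which also matches. Blood pressure increase is therefore one related event at each dose, within the 48-week study. Section 2.4 reports the reaction only for 4 of 9 subjects at 900 mg. Section 2.2 and the conclusions of 2.3 treat the same event at 600 mg as something that might occur beyond 48 weeks.

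**The case against.** The strongest reply is that blood pressure means are not the only safety output. Section 12.3 opens with adverse event tables, and the definition in 7.5 (2) covers any unfavourable sign with no blood pressure threshold. Lists for 12 subjects can be read one by one. Phase I found its 900 mg signal through adverse events despite treatment and stopping. Cardiovascular assessment also includes ECG, echocardiography, pulse wave, fundus and hormonal tests. Much analysis detail could sit in a SAP that is not at hand. All of this stands, and it rules out any claim that a real rise would be hidden.

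The protection is partial, however. The tables are specified by type and severity, not by dose at onset, although the 300 mg group moves to 600 mg at Week 8. Severity is graded by interference with daily life, so a symptomless rise may be graded mild. Also, 12.2 refers its method to a separate manual, whereas 12.3 refers to nothing further.

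A reader might infer three stronger points that the documents do not support:

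- **That affected subjects must leave.** Section 10.1 has no blood pressure criterion. Exit would be by investigator judgement or withdrawal. The phase I suspensions and stops for blood pressure are reported at 900 mg only. Here, vital signs are taken at discontinuation where possible, and subjects who stop for safety are followed as far as possible.
- **That 140/90 defines the event and ignores baseline.** The wording "If the systolic blood pressure exceeds 140 mmHg or the diastolic blood pressure exceeds 90 mmHg on two or more successive measurements" only triggers extra laboratory tests. A subject below the exclusion limit ("systolic blood pressure of 160 mmHg or higher or diastolic blood pressure of 100 mmHg or higher") could meet it with no change, but it is not an endpoint.
- **That most of the effect would be lost.** Assume baseline 130 (SD 12), a rise of 10 (SD 12), and that half of those above 140 stop and half are lowered by 10 to 20 mmHg. The observed mean is then +4.4 to +1.1. With no drug effect the same process gives −3.3 to −4.9, so the contrast is 4.4 + 3.3 = 7.7 to 1.1 + 4.9 = 6.0 of the 10 mmHg. Part of the apparent loss is an artefact of selection, and none of these inputs comes from the protocol.

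**Conclusion.** The point holds in a limited form. The visit-wise summaries in 12.3 could understate a blood pressure rise on the question Step II was designed to answer. The amount is not determinable from the protocol: in the illustration it runs from one third of a +10 mmHg mean rise (+6.7 shown) to all of it, under an assumed rise, drug effect and exit pattern. A rise as frequent as at 900 mg would almost certainly appear in the adverse event table, while one at the 600 mg phase I rate might not. Any event count at n = 12 shares that last limit. The gain from a wider count is that it also captures antihypertensive starts and stops.

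The phase I inconsistency needs no assumption. Section 2.4 omits the lower-dose related events. Section 2.2 says no serious or significant reactions occurred at 300 mg and 600 mg, so on that point it is incomplete rather than plainly false.

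Posture is a minor point. Table 2 accepts either lying or sitting blood pressure and does not require the same posture for a subject throughout, which permits avoidable noise in change from baseline.

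**What to change.** - **12.3:** add a per-subject count, by dose at onset, of subjects with any of: a confirmed rise relative to their own baseline (size and confirmation rule pre-specified by the sponsor); a start or increase of an antihypertensive; suspension or discontinuation for blood pressure.
- **12.3:** show visit summaries of change from baseline twice, once for all values and once for values before any new or increased antihypertensive, with the number of subjects at each visit. A time-to-event curve is optional with 12 subjects.
- **7.5:** have blood pressure taken in the same posture for a given subject at every visit.
- **2.2, 2.3 (conclusions) and 2.4:** reconcile the text with the phase I tables on drug-related blood pressure increases at 300 mg and 600 mg.

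The cost is wording and a little more tabulation. Blood pressure, concomitant drugs and reasons for stopping are already recorded. The risk summary becomes slightly less favourable.

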## 12.4 Pharmacokinetics analysis

Tabulate and examine the data on liver, plasma and urinary drug concentrations.

## 12.5 Analysis of TGF-α

Tabulate and examine the data.

## 12.6 The number of subjects to be registered according to the plan

12 subjects

Divide subjects into the following two groups in Step I (Week 0 to Week 8).

NIK-333 300 mg group: 6 subjects

NIK-333 600 mg group: 6 subjects

All subjects will receive 600 mg/day in Step II (Week 8 to Week 96).

[Rationale]

This clinical pharmacology study is an exploratory study aimed at investigating the changes of gene expression profiles in the liver and peripheral blood and identifying the drug response gene for NIK-333 in patients who were completely cured of HCV-positive HCC before and after 8-week repeated administration of 300 mg/day or 600 mg/day of NIK-333. The initial target sample size has been set at 6 subjects per group, considering feasibility of the study at the study center.

